## Abstract

Data concerning the combined effect of diet and exercise interventions on overall health in the elderly are scarce. The MED-E project’s primary aim is to assess the effect of the different 3-month sustainable healthy diet (SHD) and multicomponent training (MT) interventions on several health outcomes in the elderly. A quasi-experimental study assigned older adults into four groups: (1) SHD, (2) MT, (3) SHD + MT, or (4) control group (CG). The SHD intervention included a weekly offer of a mixed food supply and individual and group nutritional sessions on the principles of an SHD. The MT groups were submitted to 50-min exercise sessions three times a week. The primary outcomes were blood biomarkers and metabolic profile alterations that were assessed pre- and post-intervention. Additionally, data on dietary intake and nutritional adequacy, physical fitness, body composition and anthropometry, cognitive function, quality of life, and geographical data were assessed at the same time points. The MED-E project’s study protocol and future results will add to knowledge about the importance and beneficial contribution of combined SHD and MT interventions on healthy ageing policies.

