### 2.6. Outcome Assessments

#### 2.6.1. Primary Outcome

##### Blood-Based Biomarkers and Metabolic Alterations

Our primary outcomes concern blood-based biomarkers and metabolic alterations. At baseline and post-intervention, venous blood samples were taken. All the biochemical and metabolomic analyses—untargeted NMR—were performed in a certified laboratory. 

After an overnight fast of at least 8 h, a competent professional collected venous blood samples from the antecubital vein (required volume between 10 and 20 mL, maximum of two tubes) in a specially designated and equipped room, separating samples into serum and plasma. The following nutritional and age-related biomarkers [45] will be analysed in serum blood samples: glucose; fructosamine; insulin; cortisol; protein C-reactive (high sensitivity); vitamin B12; iron; sodium; phosphorus; calcium; magnesium; lipid profiles: total cholesterol, HDL-C, LDL-C, and triglycerides; and osmolality. Traditional biochemical parameters will be enzymatically measured [46]. LDL-C will be computed according to the Friedewald formula, estimated by subtracting HDL-C and one-fifth of the triglycerides value from the total cholesterol level [47]. 

We also intend to perform untargeted NMR-based metabolomics analyses. Plasma samples were immediately frozen at −80 °C and will remain so until analyses are conducted. Blood plasma preparation for NMR analyses will include adding saline solution (sodium chloride (NaCl) 0.9%, 10% deuterium oxide) to plasma, followed by centrifugation and transfer to 5-mm NMR tubes. The NMR analyses will be performed in a Bruker Avance III HD 600 MHz spectrometer (Bruker BioSpin, Rheinstetten, Germany) equipped with a cryoprobe using a Carr–Purcell–Meiboom–Gill (CPMG or T2-edited) pulse sequence (cpmgpr1d) [48]. For one representative sample, 2D spectra (heteronuclear single quantum coherence (HSQC) and total correlation spectroscopy (TOCSY)) will be acquired to aid in metabolite annotation.

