Multivariate analyses will be applied to discriminate between the metabolic profiles of the intervention groups, enabling the identification of the most relevant panel of spectral peaks differing between them [55]. Then, univariate statistical analyses, including hypothesis testing (ANOVA or the corresponding non-parametric test), effect size, and the area under the curve (AUC) obtained by receiver operating characteristic (ROC) analyses will be applied to test the statistical relevance of the panel of spectral peaks [55]. The metabolite annotation in NMR data will be performed. A comparison with the NMR spectral profiles of standard compounds presented in databases and the validation in 2D spectra (heteronuclear single-quantum coherence (HSQC) and total correlation spectroscopy (TOCSY)) acquired for one representative sample will be completed. In addition, the metabolic pathways altered in the groups under study will be interpreted through metabolomic pathway analyses [56].

All statistical analyses performed using the SPSS IBM Statistical Software version 25.0 (SPSS, Inc., Chicago, IL, USA) for macOS (Apple Inc., Cupertino, CA, USA) will be used for data assembly and graphical analyses.

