Some challenges to this study must be recognised. Firstly, we anticipate a potential sample with several age-related comorbidities. Secondly, the elderly tend to mainly adopt sedentary behaviours, increasing difficulties in the recruitment process. Based on differences in baseline participant characteristics, a misinterpretation of the primary outcomes and an inability to generalise the results may occur. Considering the main inclusion criteria, the different interventions cannot be generalised to other specific populations. Despite including participants with lower nutritional status or who were inactive, we cannot exclude the possibility that the participants involved in the study were more prone to healthy lifestyle behaviours. Though, this bias was minimised by excluding participants that were engaged in regular physical activity or consulting a nutritionist. Additional research will help identify the most effective diet and exercise intervention protocols for more heterogeneous, non-uniform, and other specific population groups. A cross-over and randomised controlled trial (RCT) design, where the same participant implemented different interventions, would reduce the likelihood of heterogeneity affecting the evaluation of primary outcomes. Initially, our study protocol was thought and designed to be a cross-over RCT. Although, the methodology needed to be adapted due to the beginning of the unpredictable pandemic situation, which occurred simultaneously with the start of the recruitment study and disabled the sample randomisation. The pandemic situation delayed and imposed logistical difficulties in the recruitment process. The lockdown and isolation of this at-risk population group (older adults) affected baseline assessments and the study intervention due to the closure of facilities.

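### The NMR peak panel is selected and scored by discrimination between non-randomised groups with no time, change or baseline term stated, although the primary outcome is pre-to-post metabolic alteration

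*Protocol article*

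**What the plan says.** The Abstract defines the endpoint: "The primary outcomes were blood biomarkers and metabolic profile alterations that were assessed pre- and post-intervention". Section 2.6.1 repeats it ("Our primary outcomes concern blood-based biomarkers and metabolic alterations") and gives the sampling: "At baseline and post-intervention, venous blood samples were taken". A spectrum before and after the intervention is therefore available in principle for each completer.

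The metabolomic paragraph of Section 2.7 sets out four steps:

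- **Discrimination:** "Multivariate analyses will be applied to discriminate between the metabolic profiles of the intervention groups".
- **Selection:** this step is described as "enabling the identification of the most relevant panel of spectral peaks differing between them".
- **Testing:** the selected panel goes to univariate tests (ANOVA or a non-parametric counterpart), effect sizes and ROC AUC.
- **Interpretation:** pathway analysis is used to interpret which pathways were altered in the groups.

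Earlier in the same section, the article plans a percentage change from baseline, a repeated-measures ANOVA (or non-parametric counterpart) with interactions for each dependent variable, and confounders as covariates in the ANOVA models. Section 2.6.3 lists those confounders, including clinical history and medication.

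On allocation, the Discussion states that the pandemic "disabled the sample randomisation". It also warns that baseline differences between participants may lead to misinterpretation of the primary outcomes.

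**The concern.** An alteration is a change within a person. Discrimination between groups is a different quantity: it responds to any difference between groups, including one that existed before the intervention. Under randomisation, a between-group contrast of post-intervention spectra would be free of such differences on average. Here it need not be. Section 2.1 describes recruitment through community programmes, daycare centres, municipalities, healthcare centres and social media, and the groups may differ in habitual diet, medication or comorbidity.

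If the metabolomic paragraph is followed as written, a panel of peaks that separates the groups could be reported as pathways altered by diet or exercise when those peaks had not moved. This affects a primary outcome in a study whose stated purpose is to assess the effect of the interventions.

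**Working it through.** **Step 1. Endpoint against analysis.**

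| Element | Endpoint (Abstract, Section 2.6.1) | Metabolomic paragraph, Section 2.7 | Earlier paragraphs, Section 2.7 |
|---|---|---|---|
| Time | Baseline and post-intervention | None named | Delta percentage; repeated measures |
| Contrast | Alteration | Between groups | Main effects and interactions |
| Panel selection | – | Multivariate discrimination between groups | Not addressed |
| Univariate test | – | ANOVA, not described as repeated measures | Repeated-measures ANOVA for each dependent variable |
| ROC AUC | – | Yes, input not stated | Not addressed |
| Covariates | – | None named | In the ANOVA models |

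The univariate row can be reconciled by reading the earlier paragraphs as applying to each metabolite. The selection and AUC rows cannot, because nothing earlier in the section refers to them. Selection also comes before the univariate test. A later repeated-measures test on the panel would not undo a panel chosen for prior differences, and it would not recover peaks that changed but did not discriminate.

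**Step 2. Illustration of the mechanism.** The article gives no figure for this effect, so there is none to reproduce. The only input taken from it is the sample size in Section 2.3: 25 per group with 20% dropout, which leaves 25 × 0.80 = 20 completers per group and 80 in all.

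Assumptions, none of them in the article:

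- no intervention effect;
- one peak, with SD 1;
- one of the four groups shifted by d SD at both visits;
- pre-post correlation of 0.5 or 0.7;
- no covariate adjustment.

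For a one-way ANOVA on post-intervention values, the noncentrality is n × Σ(group mean − overall mean)². The overall mean is d/4, so the sum is 3(d/4)² + (3d/4)² = 0.75d². With n = 20 this gives λ = 15d², on 3 and 76 degrees of freedom. The AUC for the shifted group against an unshifted one is Φ(d/√2).

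| d (assumed) | λ = 15d² | Rejection, post values, calculated | Rejection, post values, simulated | AUC, post values |
|---|---|---|---|---|
| 0 | 0 | 5% | 4.7–5.0% | 0.50 |
| 0.2 | 0.60 | 8.6% | 8.5% | 0.56 |
| 0.3 | 1.35 | 13.6% | 13.5–14.0% | 0.58 |
| 0.5 | 3.75 | 32.2% | 31.6–31.8% | 0.64 |
| 0.8 | 9.60 | 71.8% | 72.0% | 0.71 |

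The simulation used 20,000 runs per scenario, and ranges cover the two correlations. The same ANOVA on change from baseline rejected in 4.7–5.4% of runs across all scenarios. That follows by construction: a shift that is equal at both visits cancels in the difference. The calculation treats one peak fixed in advance and does not model the selection step.

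**The case against.** The strongest objection is that the article does not say which spectra enter the multivariate step. Post-intervention, change and paired spectra all fit the wording. A reader might infer that the plan compares post-intervention spectra only, or that it has no pre-post analysis of the metabolomic outcome. The document supports neither reading. The metabolomic paragraph never mentions post-only values. The repeated-measures and delta analyses belong to the same section, are stated for each dependent variable, and are not limited to conventional biochemistry.

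Safeguards also exist. Medication and clinical history are listed as confounders, covariates enter the ANOVA models, groups are compared at baseline, weighting is allowed, and the Discussion discloses the risk. A condensed article may also leave the input matrix of a multivariate method to a fuller document.

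Much of this stands. It rules out a flat statement that the plan estimates the wrong quantity, and it makes the rejection rates conditional on a post-only input that the article does not state. It does not dispose of the point. The article itself fixes how the panel is selected, tested and interpreted, and every step is worded as a difference between groups. No safeguard is tied to the multivariate selection or the AUC. The comparison of baseline measurements could reveal an imbalance, but no consequence for the NMR analysis is stated.

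**Conclusion.** The point holds in a limited form. For a primary outcome defined as pre-to-post alteration in a non-randomised study, the dedicated NMR analysis selects and scores peaks by group discrimination and names no time, change or baseline element. The general provisions of Section 2.7 may protect the univariate tests of single metabolites. They do not reach the selection or the AUC, so prior group differences could be reported as intervention effects.

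The size in this study is unknown. The rates of about 14%, 32% and 72% apply only if post-intervention values alone are analysed, without covariates, and with the assumed shifts of 0.3, 0.5 and 0.8 SD. The contrasting 5% on change depends on those shifts being additive and stable over time. The figures should not be read as an estimate of bias in this study. The point merits correction, since it concerns a primary outcome and, according to Section 2.6.1, the NMR analyses were still to be performed.

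**What to change.** In the metabolomic paragraph of Section 2.7, state that the multivariate selection, the univariate tests and the ROC AUC all use one of the following:

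- within-participant change (post minus baseline);
- a group-by-time contrast;
- post-intervention values adjusted for baseline.

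State that the confounders of Sections 2.6.3 and 2.7 enter the univariate metabolite models. Run the same discrimination on the baseline spectra as a negative control and report it beside the main result. Separation already present at baseline would show how much of the apparent effect predates the intervention.

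The cost is a few sentences and some extra computing, since blood is taken at both visits. Participants without paired samples would leave the main NMR analysis. The change removes stable additive differences between groups. It does not remove differential trends or regression to the mean, and the report should say so.

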Since older adults spend an average of 9.4 h/day engaged in a sedentary behaviours, which corresponds to 65–80% of their waking time [17], and are the least physically active segment of the population, engagement in physical activity (PA) routines should be considered in this age group. Exercise benefits to functional and cognitive capacities are well demonstrated in the literature [18], in addition to improvements in glycaemic control [19], inflammation [20], and body fat reduction [21]. Sampaio et al. (2019) demonstrated that regular multicomponent training (MT) sessions diminish the physiological effects of sedentary routines by improving quality of life, mobility, balance control, and bone mineral content [20], thereby delaying the development and progression of chronic and disabling conditions. Most studies regarding the impact of exercise on biomarker profiles were developed with different types of training (strength or aerobic programs). The literature shows a decrease in LDL-C, total cholesterol, CRP, IL-6, TNF-α, leptin, glycosylated haemoglobin A1c (HbA1C), insulin, and glucose, and an increase in high-density lipoprotein cholesterol (HDL-C) [22,23]. In MT programs, studies have corroborated previous findings concerning improving lipid profiles—lowering triglycerides and elevating HDL-C—and antioxidant capacity [24].

Moreover, studies regarding the combined effect of sustainable healthy dietary patterns and exercise interventions are scarce. The few existing studies suggest an intensification of the effects of isolated interventions with other beneficial health outcomes [25]. Besides the classical and standard biochemical analyses, untargeted nuclear magnetic resonance (NMR) spectroscopy-based metabolomics have begun to gain insight. This technique allows for the semi-quantification and analysis of hundreds of low molecular weight metabolites in biofluids, stools, and tissues [26,27], enabling the routine identification of novel compounds. Existing studies of diet and exercise approaches are based on short-term duration and strictly controlled and isolated diet or exercise intervention protocols, mostly with different population groups (such as children or younger adults) [28]. More extended intervention studies conducted under less strict diet and exercise programs are sparser. The qualitative and quantitative differences in metabolic profiles resulting from this combined intervention in the elderly have not yet been explored.

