### 2.7. Statistical Analyses

Descriptive results will be expressed as median and inter-quartile range (IQR) or mean and standard deviation (SD), as appropriate, for continuous variables. Discrete variables will be presented as counts and percentages. The minimum threshold value for statistical significance used will be *p* ≤ 0.05.

The normality tests, histogram, and plot distribution will assess the normality of data distribution. Comparative analyses between participants and dropouts will be realised by *t*-test or Mann–Whitney U-test for continuous variables and Pearson-Chi Squared or Fisher exact test for categorical variables to determine whether attrition bias was observed. 

Potential differences among intervention groups in baseline measurements will be evaluated using a one-way Analysis of Variance (ANOVA) or correspondent non-parametric Kruskal-Wallis test. A Pearson Chi-squared or Fisher exact test will be used for between-group comparisons of categorical variables. 

Covariates (e.g., sociodemographic and economic characteristics; clinical history, such as the presence of comorbidities; and daily physical activity) were selected a priori and tested. The confounding variables will be entered as covariates in the ANOVA models. For each model, the contribution of all covariates will be tested separately; only the ones that change the magnitude of the association by at least 10% will be included in the final models. The fit of the models will be determined. Whenever necessary, we will use weighted samples to tackle the bias imposed by differential sampling probabilities.

A delta percentage will be calculated to assess the percentage of change between baseline and post-intervention assessments. An ANOVA or correspondent non-parametric test with repeated measures will be performed for differences in main effects and interactions for each dependent variable. When significant interactions are found, Bonferroni posthoc tests will determine the origin of the differences. Multivariable regression analyses will explore the associations between blood-based markers and metabolomics and the secondary outcomes.

Geographical information systems data will be collected. The associations of the primary and secondary outcomes with environmental features will be explored through generalised linear models to understand whether built environment food and PA features lead to statistically significant differences in participants’ dietary and exercise routines.

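### NMR peaks are chosen because they separate the groups and are then tested for separating them in the same participants, so the nominal p-values and apparent AUCs for part of the primary outcome are not valid as stated

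*Protocol article*

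**What the plan says.** Section 2.7 (Statistical Analyses) gives the metabolomics analysis as an ordered procedure. Multivariate methods first discriminate the intervention groups, "enabling the identification of the most relevant panel of spectral peaks differing between them". The next sentence begins "Then, univariate statistical analyses, including hypothesis testing (ANOVA or the corresponding non-parametric test), effect size, and the area under the curve (AUC" and ends by saying that these analyses "will be applied to test the statistical relevance of the panel of spectral peaks".

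The rest of the section gives one significance rule: "The minimum threshold value for statistical significance used will be *p* ≤ 0.05". The one multiplicity correction named is tied to the repeated-measures models: "When significant interactions are found, Bonferroni posthoc tests will determine the origin of the differences". Validation is mentioned for the NMR data only in connection with metabolite annotation, using 2D spectra "acquired for one representative sample will be completed".

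The endpoint's standing is set in section 2.6.1: "Our primary outcomes concern blood-based biomarkers and metabolic alterations". Section 2.3 plans one cohort of 25 per group in four groups, with 20% dropout anticipated. The Introduction describes NMR metabolomics as allowing "semi-quantification and analysis of hundreds of low molecular weight metabolites".

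**The concern.** The second step asks of the selected peaks the question that was used to select them. A one-way ANOVA p-value is calibrated for a peak fixed without reference to the group labels. For a peak kept because its group means looked different in these participants, the null distribution is shifted towards small p-values. Effect size and AUC are biased upwards for the same reason.

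The article describes no second sample, data split or resampling, and no correction tied to peak selection. The 2D-spectra check confirms which compound a signal belongs to. It says nothing about whether the signal truly differs between groups.

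At stake is part of the primary outcome. Followed as written, the procedure would usually report some metabolic difference between groups even if neither intervention changed anything.

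**Working it through.** **Sample size used.** The plan's own figure is 25 per group. A four-group comparison with f = 0.40 (reading the stated effect size as Cohen's f), alpha 0.05 and power 0.80 needs N = 73, or 19 per group when balanced. With dropout, 19/0.8 = 23.75, so 24, which agrees with 25 after rounding. The point does not challenge that figure. It only supplies the number of completers: 25 × (1 − 0.20) = 20 per group.

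**Assumptions not in the documents.** Number of candidate peaks m: 50 to 400 (up to 500 in one set of runs). Panel size: 10. Peaks are Gaussian and independent, with within-block correlation of 0.5 tried as well. No group effect on any peak.

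**Arithmetic benchmark: peaks selected by the test statistic itself.** Under the null the number of peaks with p ≤ 0.05 is B ~ Binomial(m, 0.05), with mean 0.05m. If the 10 smallest p-values form the panel, the expected share of the panel at p ≤ 0.05 is E[min(10, B)]/10, and the chance of at least one is 1 − 0.95^m.

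| m | 0.05m | expected share | at least one |
|---|---|---|---|
| 50 | 2.5 | 25% | 92% |
| 100 | 5 | 50% | 99% |
| 200 | 10 | 88% | >99.9% |
| 400 | 20 | >99% | >99.9% |

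Simulation of that rule with the four-group F test gave 24%, 52%, 88% and 100%.

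**Closer to the plan: multivariate selection, then four-group ANOVA on the same samples.** The article names no multivariate method, so two PLS-type rules were simulated with 20 per group and a top-10 panel.

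| Selection rule | m = 50 | 100 | 200 | 400 | 500 |
|---|---|---|---|---|---|
| One-component PLS weights, share at p ≤ 0.05 | 21% | 30% | 46% | 64% | – |
| Two-component PLS-DA-type weights, share at p ≤ 0.05 (correlation 0 or 0.5) | 23–24% | 42–43% | 67–69% | – | 97% |

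The nominal share is 5%. At least one selected peak reached p ≤ 0.05 in 90–100% of runs under the one-component rule. Under the two-component rule the figures were 86–90% with 50 peaks, 99% with 100 and 100% with 200 or 500.

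**AUC, two groups, 20 per group, top 10 by mean difference.**
- Single selected peaks, same samples: mean about 0.65, 0.68, 0.70 and 0.72 for m = 50, 100, 200 and 400. The median best peak was 0.73 to 0.78.
- Single selected peaks above 0.9: at least one in 0% of runs for 50 to 200 peaks, and in 0.3% for 400.
- The ten peaks combined into one weighted score, same samples, independent peaks: 0.90 to 0.97.
- The same peaks on fresh samples (m = 50 to 500): 0.498 to 0.503 singly and 0.494 to 0.508 combined.
- Selection redone inside five-fold cross-validation: mean 0.49 to 0.51.

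The last two lines show that the excess over 0.50 comes from the selection.

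**The case against.** Several points on the other side are sound and limit the claim.

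- **Same participants.** The article does not say in words that selection and testing share samples. This is inferred from its describing one cohort and no split. It is the only reading the text supports, but it is an inference.
- **Unseen material.** The article is condensed, and section 2.7 cites a methods source for both steps. That source or a full analysis plan might add cross-validation, permutation or false-discovery control. This stands as a condition on the conclusion. Cross-validating the multivariate model alone would not repair the second step, because ANOVA p-values on a preselected panel still ignore the selection.
- **AUC.** A reader might infer that the plan would produce AUCs above 0.9 from noise. The article lists AUC among the univariate analyses, most naturally one ROC curve per peak, and gives no rule for combining peaks. The 0.90–0.97 range needs such a rule.
- **Worst-case p-values.** Selecting by the F statistic and then testing with it gives the largest inflation. The article says that a multivariate method selects, so the PLS-type figures are the fairer guide.
- **Peak count.** The mention of hundreds of metabolites describes what the technique can do, not how many signals this study will analyse.
- **Reach.** A reader might infer that NMR is half of the primary outcome, or that the pathway analysis is fed by the selected panel. The article gives no weights to the primary domains and does not state the pathway input.
- **Discovery work.** Untargeted metabolomics is exploratory, and labelling the results descriptive would largely cure the problem. That is true, but the article calls the step a test of relevance and places the endpoint among the primary outcomes.

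**Conclusion.** The point holds in a limited form. It concerns a stated procedure, not a detail left out: peaks are chosen for differing between groups and then tested for differing, with p ≤ 0.05 as the only threshold. Unless material not shown corrects for the selection, the nominal p-values, effect sizes and apparent AUCs of the panel are not valid evidence for this part of the primary outcome.

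With no true effect, 20 completers per group and 10 peaks taken from 50 to 400 independent candidates, about 20–65% of peaks chosen by one-component PLS weights reach p ≤ 0.05 instead of 5%. The share is higher with two components, or if the test statistic itself does the selecting. At least one peak is declared in about 90–100% of runs. Single-peak two-group AUCs average about 0.65–0.72 instead of 0.50.

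The exact size depends on the peak count, panel size and selection rule, none of which the article gives. The direction was the same in every setting tried. The documents do not support a claim that AUCs above 0.9 would follow from the plan as written.

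**What to change.** - Test every retained peak, not only the selected panel, for between-group differences in baseline-to-post change, with Benjamini–Hochberg false-discovery control over all peaks.
- Report multivariate discrimination and AUC only from cross-validation in which peak selection is redone inside each fold, with a p-value from permuting the group labels.
- Base any pathway interpretation on the false-discovery-controlled results.
- At minimum, label the panel's p-values, effect sizes and AUCs as descriptive and drop the description of this step as a test.

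If an existing analysis plan already does this, a sentence in section 2.7 saying so would settle the point.

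The cost is a little more analysis code and fewer peaks declared. No new samples are needed, and section 2.6.1 describes the NMR analyses as still to be done.
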